### Issues of Engagement in App-Based Mental Health Interventions

Despite their feasibility and empirical support, there are significant concerns regarding treatment engagement in app-based mental health interventions. Enrollment rates are low, with a meta-analysis showing that 8% to 58% of participants never download the intervention app [49]. Even when the app is downloaded, studies show that some users never use it, and those who engage with the app are unlikely to do so more than a few times, showing a decrease in use over time [49,50]. Similarly, attrition rates range from 24% to 53%, with higher rates found in longer programs (ie, more than 8 weeks) [49]. Importantly, programs without guidance (eg, via human coach, automated reminders) seem to lead to even poorer treatment engagement [51]. This limited treatment engagement in app-based mental health interventions is concerning as users may not receive enough treatment dosage to promote behavioral change.

Considering the importance of promoting treatment engagement for the success of app-based interventions, researchers and clinicians have proposed multiple strategies to increase acceptability, improve adherence, and reduce attrition. Among numerous approaches to promote app user engagement, cultivating a sense of guidance and support may be especially effective. Onboarding procedures in which users interact with providers before starting the intervention, asking questions about the intervention, problem-solving potential barriers to engagement, and building a relationship with the team have shown to be associated with higher treatment engagement [52]. Similar procedures in app-based interventions for POC seem to be effective as users can ask questions about the program and request assistance with technology [53]. As a whole, studies show that onboarding procedures decrease treatment attrition in app-based mental health interventions [49].

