Those individuals who meet eligibility criteria will be contacted by a research team member to obtain verbal consent and randomize them to either the intervention group (n=40) or a wait-list control group (n=40) using block randomization. During this onboarding procedure, participants in the intervention group will be assisted in installing the mindfulness meditation app, setting app notifications, understanding daily text messaging reminders, and getting familiar with the intervention content. Similar onboarding procedures have been shown to improve treatment adherence in app-based mindfulness meditation studies [49,51]. Participants in the control condition will be reminded of the scheduled assessments and when they will receive access to the mindfulness meditation app (ie, 4 weeks after randomization). Individuals who endorse self-harm or suicidal ideation during the onboarding procedure or in their replies to the text messages will be further assessed and referred to crisis support services.

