### Mindfulness Meditation Intervention

This study will use the Ten Percent Happier app, a consumer-based mindfulness meditation app that offers a wide range of meditation practices developed and guided by renowned experts in the field. Among the many mindfulness apps available in the market, we chose this app because it has been shown to be an effective intervention to increase mindfulness and decrease anxiety and depressive symptoms in previous studies [60-62]. It is important to note that samples in these studies were almost exclusively non-Latinx White.

The intervention will consist of using the Ten Percent Happier app to complete at least 1 meditation daily—with the possibility of exceeding this goal by choosing additional meditations—for 4 weeks. More specifically, participants will be asked to complete The Basics and The Basics II courses to familiarize themselves with the principles of mindfulness meditation. Each audiorecorded session begins with a short video providing psychoeducation around mindfulness meditation and teaching specific techniques (eg, using the breath as an anchor, redirecting attention, noting thoughts and emotions). These 2 introductory courses comprise 15 sessions, in which the meditation length gradually increases from 5 to 17 minutes. For the last 2 weeks of the program, participants will be invited to complete the Essential Advice course, which dispels common myths around mindfulness meditation (eg, “meditators empty their minds,” “successful meditations are those without distractions”) and teaches participants how to deal with common obstacles in their practice (eg, difficult emotions, strong physical sensations). This additional course comprises 14 sessions ranging in length from 15 to 18 minutes. For any additional practice, participants will be able to select any meditation from the Ten Percent Happier library based on their preferences. This highly structured 4-week introductory course may be more likely to provide the foundation necessary for participants to benefit from mindfulness meditation compared with less structured programs often seen in app-based mindfulness meditation research [46]. Moreover, short-term app-based mindfulness meditation interventions (ie, 4 weeks or less) lead to lower attrition rates compared with longer programs [49].

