##### Treatment Adherence

Number of meditations completed, number of days with at least one meditation completed, and total time meditated in minutes will be used as behavioral measures of treatment adherence. This information is tracked by the Ten Percent Happier app and will be obtained by asking participants in the intervention group to share a screenshot of their app profile via text message. Previous studies have shown that this methodology allows researchers to obtain accurate behavioral indicators of treatment adherence [60,77]. These behavioral indicators will be collected at midtreatment and posttreatment.

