## Results

Recruitment began in October 2021. This study will use multilevel modeling, a statistical methodology that allows time-varying predictors and handling dependence among repeated observations. We will examine changes in primary outcomes (ie, stress, anxiety, depression), hypothesized mediators (ie, mindfulness trait, self-compassion, experiential avoidance, rumination, emotion suppression), and treatment effects from baseline to midtreatment and posttreatment, and from midtreatment to posttreatment within each group. Test of mean differences will be calculated by fitting models with group condition (ie, intervention vs control) as the predictor, time as a within-group factor (ie, baseline, midtreatment, posttreatment), and a group-by-time interaction. To explore whether changes in primary outcomes are mediated by changes in the hypothesized mechanism of change, we will conduct mediation analyses. Relevant demographic variables (eg, income, age, gender) will be added to the models as covariates. These models will include random intercepts to capture potential differences in the starting points of each outcome and an autoregressive error structure to account for dependence among repeated measures. Given the relatively small sample size in this study, random slopes will be fitted when possible. Although our primary interest is in group-by-time interactions corresponding to differential treatment effects, should significant interactions or main effects be found, follow-up contrasts can be used to examine within-group changes over time and between-group differences at each time point.

Considering issues of attrition and their potential effects on statistical significance and treatment effect sizes in app-based mindfulness meditation research [49], we will examine data using both intention-to-treat and per-protocol analyses [78]. In intention-to-treat analyses, group comparisons include all patients originally allocated after randomization, regardless of participant adherence to the intervention or withdrawal. Missing data will be handled using the last-observation-carried-forward method, which is considered a conservative approach. In per-protocol analyses, group comparisons include only those participants who completed the treatment as planned originally. Measures of treatment acceptability, satisfaction, and adherence will be examined by calculating descriptive statistics.

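### The per-protocol comparison selects on completing a treatment that only the intervention arm has, so it is not protected by randomization and can show a benefit when the app has no effect

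*Protocol article*

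**What the plan says.** The Results section of the protocol article announces that "we will examine data using both intention-to-treat and per-protocol analyses" and gives attrition as the reason. Intention-to-treat is defined so that "group comparisons include all patients originally allocated after randomization, regardless of participant adherence to the intervention or withdrawal". Per-protocol is defined so: "In per-protocol analyses, group comparisons include only those participants who completed the treatment as planned originally". The article does not rank the two analyses.

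Three other places bear on what completing treatment can mean:

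- Mindfulness Meditation Intervention: participants are to "complete at least 1 meditation daily" for 4 weeks, working through named courses.
- Treatment Adherence: the app-use data "will be obtained by asking participants in the intervention group to share a screenshot of their app profile via text message".
- Participants and Procedures: controls receive the app 4 weeks after randomization, which is also the time of the posttreatment assessment.

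**The concern.** During the comparison period a wait-list participant has no study treatment to complete, and nothing is recorded that shows who among the controls would have completed it. Taken literally, the rule leaves no controls. To yield a group comparison at all, controls must be admitted on some other criterion. The intervention arm is then filtered on behaviour after randomization and the control arm is not filtered on the same thing.

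If people who keep up the practice are also those who would have improved anyway, the retained intervention group looks better for reasons unrelated to the app. The article itself expects low use ("those who engage with the app are unlikely to do so more than a few times"), so the retained group could be small and strongly selected. If intention-to-treat were null and per-protocol positive, the second result would invite the reading that the app works for those who use it, and nothing in the article says which result governs.

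**Working it through.** **Stated figures.** The article gives no figure for the per-protocol analysis. Its power statement (Participants) supplies two inputs: an effect of d = 0.2 and a correlation of 0.60 among repeated measures. The stated n = 54 reproduces (power 0.954, with alpha 0.05 assumed) when 0.2 is entered as Cohen's f. Converting d = 0.2 to f = 0.1 gives power 0.41 at 54. That is a separate matter; here 0.2 serves only as a benchmark, read as a difference in baseline SD.

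**Inputs.**
- 40 per arm (Participants).
- Change SD with correlation 0.60: √(2 × (1 − 0.60)) = 0.894 baseline SD.
- Share of the intervention arm retained: 76% and 47%, from 1 − 0.24 and 1 − 0.53. The article cites attrition of 24% to 53%, and these shares stand in for the unknown completion rate. 50% is added as a middle case. In a group of 40 these are 30, 19 and 20 people.
- Correlation r between adherence and natural improvement: not in the article. Assumed, and ranged from −0.3 to 0.5.
- Controls: all kept. Also an assumption, since the article does not say.

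**Closed form at 50% retained, r = 0.3.** The mean of the upper half of a standard normal is 0.798. Spurious difference in change = 0.798 × 0.3 × 0.894 = 0.21 baseline SD.

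**Simulation with no app effect** (40,000 trials per setting, two-sided t-test at 5% on baseline-to-posttreatment change). Each cell gives spurious benefit in baseline SD, then type I error.

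| Retained | r = −0.3 | r = 0 | r = 0.1 | r = 0.2 | r = 0.3 | r = 0.5 |
|---|---|---|---|---|---|---|
| 76% | −0.11; 8.2% | 0.00; 5.1% | 0.04; 5.4% | 0.07; 6.3% | 0.11; 8.1% | 0.19; 14.1% |
| 50% | −0.21; 13.5% | 0.00; 5.0% | 0.07; 6.0% | 0.14; 8.4% | 0.21; 13.5% | 0.35; 30.3% |
| 47% | −0.22; 14.2% | 0.00; 4.8% | 0.07; 5.9% | 0.15; 8.8% | 0.22; 14.0% | 0.37; 31.6% |

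When the same selection is applied to both arms, the bias is about 0 and type I error is 4.8% to 6.1% in every setting. The bias therefore comes from the mismatch in selection between the arms. That remedy is not available in the trial, because the control counterpart is not observed.

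**Would restricting controls to survey completers help?** This was not simulated. Answering a paid online questionnaire three times is a much weaker demand than a month of meditation, and intervention participants face the survey demand as well. Such a restriction could narrow the mismatch but would not remove it.

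**Does the planned model remove it?** The group-by-time model compares changes, so stable baseline differences alone do no harm. The selection here is on change itself, which the model does not correct.

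**The case against.** The strongest reply has four parts.

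1. *The article does not say that non-adherers are dropped from one arm while all controls stay.* This is correct. A reader might infer it, but the rule for controls is simply not stated, and since attrition is the motive, controls who miss assessments might be excluded too. The simulation's retention of all controls is an assumption. The point survives because no available control rule matches selection on completed treatment.

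2. *It is not shown that the analysis will produce a benefit.* Also correct. The article gives no link between adherence and symptom change. The bias is zero if there is none and favours the control arm if the link is negative. Demographic covariates in the planned model might absorb part of it, and the simulation has none. The error rates are illustrations, not forecasts for this trial.

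3. *Ranking the analyses, setting an adherence cut-off and stating how controls enter are details that an article may leave to the full protocol or analysis plan.* This stands, and those omissions are not the complaint. The complaint is about what the article does fix: a group comparison restricted by completion of a treatment that one arm lacks. A reader might also take the side-by-side presentation to mean equal standing with intention-to-treat; the text does not say that either.

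4. *Completing as planned need not mean meditating every day.* It could mean finishing the named courses or staying in the programme, and three adherence measures are listed without a choice among them. So the article does not support a claim that hardly anyone would qualify. Each of these definitions still selects on behaviour seen only in the intervention arm.

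**Conclusion.** The point holds in a limited form. The per-protocol comparison conditions on behaviour after randomization that exists and is measured in one arm only, so it can show a benefit with no app effect. At an assumed correlation of 0.3 the spurious benefit is 0.11 to 0.22 baseline SD with type I error 8% to 14%, which spans the stated planning effect of 0.2. Over 0 to 0.5 the range is 0 to 0.37 SD and about 5% to 32%. These figures assume that all controls are kept and that 47% to 76% of the intervention arm is retained.

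A positive correlation is plausible if motivated people improve more anyway, but neither its sign nor its size is established by the document, so it would be wrong to say that the analysis is bound to favour the app. The planned intention-to-treat comparison of everyone allocated is free of this selection. The trial therefore has a sound basis for its conclusion, provided the plan says that this is the basis.

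**What to change.** State that the intention-to-treat group-by-time comparison alone supports the conclusion on effectiveness. Then do one of two things.

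**Replace the per-protocol contrast** with a complier-average causal effect using randomization as the instrument: the intention-to-treat effect divided by the proportion of the intervention arm who used the app at all, meaning at least one completed meditation. The number of meditations completed is already collected. A higher cut-off on days meditated should not define compliance here, because it assumes no effect in partial users. As an assumed example, let half adhere with effect 0.4 and half use the app partly with effect 0.2. Intention-to-treat is 0.5 × 0.4 + 0.5 × 0.2 = 0.3. Dividing by the 0.5 above the cut-off gives 0.6, against a true 0.4. Counting any use gives 0.3 / 1 = 0.3, the correct average over users. For missing screenshots, report bounds: all such people counted as users, then all as non-users.

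**Or keep per-protocol as supportive only**, labelled as a non-randomized comparison open to selection bias.

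The cost is a few lines of analysis code and no change to conduct. The complier-average interval is wider. If the 8% to 58% never-download range cited in the article applied, the proportion using the app would be at most 0.92 to 0.42, so estimate and interval would grow by at least 1/0.92 = 1.09 to 1/0.42 = 2.38 times; assisted installation should help. Two assumptions need stating: onboarding and text reminders do not affect people who never use the app, and controls do not obtain the app on their own before week 4.

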## Discussion

### Principal Findings

Despite extensive evidence showing the negative mental health effects of race-related stress in POC [6-11,14-17] and the promise of mindfulness meditation to help these individuals cope [20-24,26,30-32,79], this evidence-based treatment continues to be understudied among this high-risk population in both traditional [30,35,36] and digital formats [46-48]. As such, this study seeks to address gaps in the literature by (1) recruiting a sample exclusively composed of POC who report elevated levels of race-related stress and (2) testing the acceptability and effectiveness of a self-guided app-based mindfulness meditation intervention.

The main goal of this study is to determine whether POC who receive this self-directed app-based mindfulness meditation intervention experience reductions in mental health symptoms often associated with experiencing race-related stress. Based on previous meta-analyses [46,47,79], we hypothesize that POC who receive the intervention will experience significant decreases in overall stress, anxiety, and depression compared with those in the control group.

An additional goal of this study is to examine whether this self-directed app-based mindfulness meditation program engages potentially relevant clinical targets for POC exposed to race-related stress. Based on previous meta-analyses [20-24], we hypothesize that POC who receive the intervention will experience significant increases in mindfulness and self-compassion compared with those in the control group. Although increases in mindfulness are a well-established mechanism of change in mindfulness meditation programs, the role of self-compassion is less understood, warranting further investigation [20,21,23,24]. Considering previous studies showing the crucial role of experiential avoidance [80,81], rumination [20,23,24,82,83], and emotion suppression [29,83,84] as mediators in the development of mental health problems among individuals exposed to stressors related to race, we hypothesize that POC who receive the intervention will experience significant decreases in these 3 variables compared with those in the control group.

Although mediation analyses are exploratory in nature, given the relatively small sample in this study, we hypothesize that changes in the secondary outcomes (ie, mindfulness, self-compassion, experiential avoidance, rumination, emotion suppression) will mediate changes in the primary outcomes (ie, stress, anxiety, depression). These analyses will provide novel information regarding potentially meaningful mechanisms of change in mindfulness meditation interventions among POC exposed to race-related stressors.

Finally, information regarding treatment acceptability, satisfaction, and perceived appropriateness may be especially important, given researcher and clinician concerns regarding potential cultural mismatches between mindfulness meditation and the needs of POC [32,85]. Similarly, data on treatment adherence in self-directed app-based mindfulness meditation are crucial to understanding whether this digital approach can indeed reduce unmet mental health need among POC while capitalizing on technology already available in households with more limited technological device ownership [40]. Issues of treatment adherence are significant considering extensive evidence of low enrollment, poor use, and high attrition rates in self-directed app-based interventions [49-51]. As such, descriptive information regarding number of individuals enrolled versus those eligible, number of meditations completed, total time meditated in minutes, survey completion rate, and number of dropouts is essential to determine the feasibility of this type of program and the potential impact of the engagement strategies used in this study (ie, short program length, onboarding procedure, text messaging reminder system, app notifications, financial incentives).

### Conclusion

To our knowledge, this will be the first study to include a sample of exclusively POC presenting with elevated levels of race-related stress, contributing to the nascent data on the acceptability and effectiveness of self-directed app-based mindfulness meditation among marginalized groups. This study may help reduce disparities in mindfulness meditation among POC by testing an innovative delivery method and identifying relevant clinical targets for this at-risk population. Findings from this study could also inform the design of future studies using methodologies that provide more nuanced information about contextual and cultural factors influencing the success of digital mindfulness meditation interventions among POC (eg, qualitative, mixed methods). Similar approaches have provided relevant data on factors facilitating the provision of traditional face-to-face mental health services for communities of color [86]. This line of research is necessary to guarantee that app-based interventions for POC attend to issues of diversity, equity, and inclusion, reducing inequities already present in brick-and-mortar mental health services [43].

## Abbreviations

APOI: Attitudes Toward Psychological Online Interventions
ERQ: Expressive Suppression of the Emotion Regulation Questionnaire
GAD-7: General Anxiety Disorder
IRRS-B: Race-Related Stress–Brief
MAAS: Mindful Attention Awareness Scale
MDM: Multicultural Discrimination Module
PHQ-8: Patient Health Questionnaire
POC: people of color
PSS: Perceived Stress Scale
RCT: randomized controlled trial
RRS-SF: Ruminative Response Scale, short form
SCS-SF: Self-Compassion Scale–Short Form
